## Abstract

Globally, India is the second largest consumer of tobacco. However, Indian medical students do not receive adequate training in smoking cessation counseling. Each patient hospitalization is an opportunity to counsel smokers. Medical Student Counseling for Hospitalized patients Addicted to Tobacco (MS-CHAT) is a 2-arm multicenter randomized controlled trial (RCT) that compares the effectiveness of a medical student-guided smoking cessation program initiated in inpatients and continued for two months after discharge versus standard hospital practice. Current smokers admitted to the hospital are randomized to receive either usual care or the intervention. The intervention group receives inpatient counseling and longitudinal postdischarge telephone follow-up by medical students. The control group receives counseling at the discretion of the treating physician. The primary outcome is biochemically verified 7-day point prevalence of smoking cessation at 6 months after enrollment. Changes in medical student knowledge and attitude will also be studied using a pre- and postquestionnaire delivered prior to and 12 months after training. This trial tests a unique model that seeks to provide hands-on experience in smoking cessation counseling to medical students while simultaneously improving cessation outcomes among hospitalized smokers in India.

## 1. Introduction

Global Adult Tobacco Survey (GATS) 2016 showed that India had 100 million smokers [1]. Smoking cessation substantially reduces the risk of death associated with smoking, and interventions to quit smoking are both efficacious and cost-effective [2, 3]. Studies have shown that counseling hospitalized patients is effective if started during hospitalization and continued for at least a month after discharge [4]. However, numerous barriers exist to widespread adoption of this practice [5].

Most physicians lack the necessary knowledge and skills to offer effective cessation counseling to their patients [6, 7]. This gap likely starts from medical school [8]. Purely didactic-based teaching may not be sufficient in preparing students for independent practice, particularly if inadequately supplemented with the varied experience of counseling actual patients [9]. Educational interventions have been found to have greater student engagement when they include a component of integrative learning, such as in a real patient encounter [10].

We designed the current study to test the hypothesis that utilizing trained medical students to counsel hospitalized smokers will lead to an increase in patient quit rates, while also improving medical student knowledge and confidence regarding smoking cessation counseling.

## 2. Materials and Methods

The Medical Student Counseling for Hospitalized patients Addicted to Tobacco (MS-CHAT) study protocol received institutional approval from the institutional review board at University Hospitals/Case Western Reserve University, USA, as well as the sites in India. The trial was registered in the https://clinicaltrials.gov/ database on 10 May 2018 (NCT03521466). The trial started recruiting in December 2018. It is expected to continue until July 2021. All patients enrolled in the trial will provide written informed consent. The operational definitions for the terms used in the methods and outcome sections are given in Table 1.

### 2.1. Medical Student Education

#### 2.1.1. Participants

Second-year students from three different medical schools (Figure 1) are called upon to volunteer for the program, with 30 students from each school enrolled in the study. These medical schools train between 150 and 250 students in each class. The medical school course in the participating medical schools is of 5.5-year duration. Medical and surgical clinical rotations start during the students' second year with case-based discussion, tailored to the level of training.

#### 2.1.2. Training

The training modules were developed by adapting the WHO guide for tobacco cessation counselors to the Indian context. The content predominantly addresses the skills of behavioral counseling. The training consists of a three-hour didactic lecture, followed by group role-playing scenarios for two hours, with peer and proctor feedback. Following training, the students are asked to complete a knowledge questionnaire. Students are selected for the second part of the trial (patient counseling phase) once they obtain a minimum test score.

### 2.2. Patient Counseling

The structure of the study is described in Figure 2.

#### 2.2.1. Trial Design and Participants

This is an open-label, two-armed, parallel-group, block randomized controlled trial with 1 : 1 concealed allocation. Patients are the unit of randomization. Eligibility criteria include age 18-70 years, active admission to the hospital, and current smoking or report having smoked in the last four weeks prior to admission (to account for changes in behavior during illness). Eligible patients are stratified based on the medical school and block randomized into an intervention or control group using a block size of 20. Opaque envelopes developed by the research team are provided to the coordinators to be used for randomization.

Exclusion criteria include patients using only nonsmoked tobacco and those who are daily alcohol users or daily drug users. Patients deemed unable to follow-up, either because of distance from the hospital or because of psychiatric, social, or medical factors, will be excluded. Patients currently participating in another tobacco cessation program are also excluded.

#### 2.2.2. Intervention Group

Participating medical students offer inpatient counseling to patients in the intervention group once during their hospitalization (recommended duration of 15-20 minutes). The medical students then follow-up with their patients and provide telephone counseling (a minimum of three sessions of 15 minutes each, over two months).

#### 2.2.3. Control Group

Smoking cessation advice is left to the discretion of the treating physician, to reflect usual care.

### 2.3. Data Collection

A study coordinator, who is blinded to group assignment, will collect follow-up information from patients in both the intervention and control groups at six months after enrollment. Patients who claim to have stopped smoking (not a single puff in the last seven days) at six months will be called in for an exhaled breath carbon monoxide (CO) test. The follow-up procedure will be identical in both groups.

Focus group discussions will be conducted among patients at the end of the trial to analyze patient knowledge, attitudes, and behaviors towards smoking cessation. Focus group discussions of students will also be conducted to qualitatively understand their experience of the program.

### 2.4. Study Outcomes

The primary outcome measure will be a biochemically verified seven-day quit rate at six months from enrollment. The criteria for a verified quit attempt will be an exhaled CO level of <10 PPM. The participant is blinded to the definition of the primary outcome (biochemically verified seven-day quit rate) until the follow-up visit is underway. Planned secondary and descriptive outcomes are listed in Tables 2 and 3, respectively.

### 2.5. Sample Size and Statistical Analysis

We calculated the sample size needed for a study with a power of 85%, *α* of .05 to detect a 10% absolute difference in the primary outcome assuming a control quit rate of 20%. This was based on a prior meta-analysis of tobacco cessation interventions among hospitalized smokers [4]. We assumed an attrition rate of 20%. Based on these calculations, a sample size of 830 patients will be required, resulting in 415 patients in the intervention and a similar number of patients in the control group.

The primary outcome will be analyzed by an intention-to-treat approach. Patients lost to follow-up at any time point will be considered as smokers for analysis. A secondary analysis with smoking status at last phone contact will be performed.

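### The stated 85% power does not match the stated primary analysis: 830 is sized as if the 20% lost left the analysis, but they are kept in as smokers

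*Protocol article*

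**What the plan says.** All the relevant statements are in the protocol article, section 2.5 (Sample Size and Statistical Analysis).

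- **Target.** The trial is sized at 85% power and alpha .05 "to detect a 10% absolute difference in the primary outcome", with a control quit rate of 20%, so 20% versus 30%.
- **Attrition and total.** "We assumed an attrition rate of 20%. Based on these calculations, a sample size of 830 patients will be required", that is, 415 per arm.
- **Analysis.** The primary outcome is analysed by intention to treat, and "Patients lost to follow-up at any time point will be considered as smokers for analysis".

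The section does not state the sample-size formula, the sidedness of the test or how attrition was brought in. It also does not say whether 20% and 30% are rates among patients followed to six months or rates among all randomised patients with losses counted as smokers.

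**The concern.** Dividing a sample size by one minus the attrition rate replaces patients who will contribute no outcome. Under the stated primary analysis no patient is in that position: each lost patient contributes an outcome, namely smoking. Losses therefore do not shrink the analysed sample. If the planning rates refer to patients followed up, losses pull both rates, and the difference between them, towards zero. If the planning rates already include losses as smokers, losses change nothing and there is nothing to inflate for.

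Either way, the 85% belongs to an analysis that the trial will not use as primary. At stake is the yardstick against which the result is read: whether the trial was built to see a 10-point or an 8-point difference in the analysed outcome, and with what power.

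**Working it through.** **Inputs** (section 2.5, with 1:1 allocation from section 2.2.1): alpha 0.05, taken as two-sided because that reproduces the total; power 85%; 20% versus 30%; attrition 20%; 830 in total, 415 per arm.

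**Step 1. Reproduce 830.** Two-proportion formula with unpooled variance:

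n per arm = (1.960 + 1.036)² × (0.20×0.80 + 0.30×0.70) / 0.10² = 8.978 × 0.37 / 0.01 = 332.2

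332.2 / 0.80 = 415.25 per arm, or 830.5 in total. This agrees with the article's 415 and 830. The pooled-variance formula gives 336 per arm, and 336 / 0.80 = 420 per arm, or 840. Without any inflation the total would be about 664 (unpooled) to 672 (pooled), so the 20% was clearly added on top.

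**Step 2. What the 85% refers to.** With 332 per arm compared at 20% versus 30%, power is 84.7% (pooled) or 85% (unpooled, by construction). The stated power is that of an analysis restricted to the 80% followed up.

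**Step 3. Power of the stated analysis.** All 415 per arm are analysed, losses count as smokers, and attrition is assumed equal in both arms.

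*Reading (a): 20% and 30% are rates among patients followed up.* The analysed rates are 0.80 × 20% = 16% and 0.80 × 30% = 24%, a difference of 8 points.

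- Standard error under the alternative: √[(0.16×0.84 + 0.24×0.76) / 415] = √(0.3168 / 415) = 0.02763
- Unpooled: 0.08 / 0.02763 − 1.960 = 0.936, power 82.5%
- Pooled: (0.08 − 1.960 × √(0.32 / 415)) / 0.02763 = 0.926, power 82.3%

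*Reading (b): 20% and 30% already count losses as smokers.* The analysed rates stay at 20% and 30%.

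- Standard error under the alternative: √(0.37 / 415) = 0.02986
- Unpooled: 0.10 / 0.02986 − 1.960 = 1.389, power 91.8%
- Pooled: (0.10 − 1.960 × √(0.375 / 415)) / 0.02986 = 1.376, power 91.6%

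| Analysis at the planned size | Rates compared | n per arm | Power (pooled) |
|---|---|---|---|
| Lost patients excluded (what 830 implies) | 20% v 30% | 332 | 84.7% |
| Lost = smoker, reading (a) | 16% v 24% | 415 | 82.3% |
| Lost = smoker, reading (b) | 20% v 30% | 415 | 91.6% |

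**Step 4. Sensitivity of reading (a) to attrition.** Pooled power at 415 per arm is 87.5% at 10% attrition, 85.1% at 15%, 82.3% at 20%, 79.2% at 25% and 75.7% at 30%. The stated 85% is met at about 15% attrition, not at the assumed 20%.

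**The case against.** **The text may lean towards the favourable reading.** The difference is described as one in the primary outcome, and the next paragraph says that outcome is analysed with losses as smokers. Taken literally, that is reading (b): the inflation is merely superfluous and power exceeds the target. This stands as a reason not to claim a shortfall. It does not rescue the stated figure, because on reading (b) the 20% attrition has no place in the calculation, yet 830 depends on it.

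**The gap is small even on the unfavourable reading.** It is 2.7 points (2.5 unpooled). With 415 per arm and a 16% control rate, the difference detectable with 85% power is 8.3 points rather than 8.0. Among patients followed up, that corresponds to about 30.4% versus 20% instead of 30% versus 20%. This is well within the uncertainty of the planning guesses, and a null result would in any case be read mainly from its confidence interval. This stands, and it limits the weight of the point.

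**The method is inferred.** The article gives no formula. Inflating the pooled figure by multiplying by 1.2 gives 808, also not far from 830. That matters little: every route that comes near 830 from the stated inputs adds patients for attrition, and the power in step 3 depends only on the 415 per arm and the analysis rule.

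**A stronger reading to avoid.** A reader might infer that the trial is underpowered, or that power falls much further because self-reported quitters who miss the carbon monoxide visit would also count as smokers. The documents support neither. They do not settle on reading (a). They give no rate for missed visits, and they do not say whether the 20% attrition already includes them.

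**Conclusion.** The stated 85% is wrong for the stated primary analysis, in a direction that the article leaves open. Power at 415 per arm is about 82% for 16% versus 24% if the planning rates describe patients followed up, and about 92% for 20% versus 30% if they already count losses as smokers. In the second case about 664 to 672 patients would have given 85%.

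This rests on a two-sided test, 20% attrition in each arm and large-sample formulas without continuity correction, which are the formulas that reproduce 830. With a continuity correction the two figures would be 79.9% and 90.2%, but that correction with the same division by 0.80 gives 888, not 830.

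The point is an inconsistency within one section and a modest correction to a stated figure. It does not touch the primary outcome, the analysis rule, the type I error or enrolment.

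**What to change.** Keep the total at 830. In section 2.5, state whether 20% and 30% are rates among patients followed up or among all randomised patients with losses counted as smokers, and replace the power statement with the one that matches:

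- *Rates among those followed up:* with 415 per arm and the 20% lost counted as smokers, the trial has about 82% power to detect 16% versus 24% verified abstinence at six months, an 8-point difference in the analysed outcome.
- *Rates with losses already counted as smokers:* with 415 per arm the trial has about 92% power to detect 20% versus 30%. Say that the total exceeds what 85% power needs, and no longer present the attrition allowance as a requirement of the calculation.

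Name the formula and the sidedness in the same place, and discuss the primary result against the restated difference. The cost is one or two sentences and no extra patients. On the first reading the quoted power becomes slightly less favourable; on the second it becomes more so.

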**Figure 2 fig2:**
[figure not shown]
Structure of study.

**Table 1 tab1:** Definitions.

7-day quit rate: defined as the patient's self-reported smoking behavior in the last 7 days. Assessed as “Have you refrained from smoking during the past seven days, and not smoked even one puff?”
Continuous abstinence: defined as being abstinent from smoking for at least the prior 90 days. Patients will be asked to specify quit date or number of weeks/months since quitting.
Biochemical testing: breath carbon monoxide < 10 PPM constitutes a verified successful quit attempt.
Previous quit attempt: a 24-hour quit attempt in the past 12 months.

**Table 2 tab2:** Planned secondary outcomes.

Patient outcomes:
(i) Biochemically verified 90-day quit rate, measured 6 months after enrollment. (ii) Number of patients achieving a 50% reduction in the number of cigarettes/bidis smoked in a week, measured at 2 and 6 months after enrollment. (iii) Correlation between verified quit rates at 6 months and FTND scores at enrollment. (iv) Correlation between verified quit rates at 6 months and number of quit attempts, by the study group. (v) Number of patients who report having quit smoking in the last 7 days at 2 and 6 months from enrollment (irrespective of biochemical verification). (vi) Agreement between self-reported 7-day quit rate and biochemically verified 7-day quit rate, measured at 6 months from enrollment. (vii) No. of patients who have refrained from using smokeless tobacco in the last 7 days, measured at 6 months from enrollment. (viii) Per protocol analysis of the 7-day quit outcome, 6 months after enrollment. Patients in the intervention arm who did not receive a hospital counseling session and at least two follow-up phone calls will be excluded.
Medical student outcomes:
(i) Pre-post analysis of medical student knowledge about counseling techniques and pharmacotherapy before, 6 weeks, and 12 months after training. (ii) Correlation between scores on the knowledge survey with patient quit rates. (iii) Qualitative analysis of the effectiveness of the training modules assessed by student survey, administered 6 weeks after training. (iv) Qualitative analysis of student attitudes towards smoking cessation counseling as assessed by a survey, administered 12 months after training. (v) Qualitative analysis of the trial design and implementation as assessed by a survey administered 12 months after training.

**Table 3 tab3:** Planned descriptive outcomes.

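### The sample size of 830 makes no allowance for intervention patients sharing at most 90 student counsellors; the cost in power is modest and depends on an unstated ICC

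*Protocol article*

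**What the plan says.** Section 2.5 sizes the trial at 85% power and alpha 0.05, "to detect a 10% absolute difference in the primary outcome assuming a control quit rate of 20"%, with 20% attrition. It concludes that "a sample size of 830 patients will be required, resulting in 415 patients in the intervention", and a similar number in the control group. No ICC, design effect or cluster size is mentioned. The primary analysis is by intention to treat with lost patients counted as smokers; no test, model or variance estimator is named.

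Delivery of the intervention is described elsewhere:

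- Section 2.1.1: three medical schools take part, "with 30 students from each school enrolled in the study". Section 2.1.2 adds that only students who reach a minimum test score go on to counsel, so 90 is a ceiling.
- Section 2.2.2: "Participating medical students offer inpatient counseling to patients in the intervention group once during their hospitalization"; the students then telephone the patients they have counselled over two months.
- Section 2.2.3: control patients receive whatever advice the treating physician chooses to give.
- Section 2.2.1: patients are randomised individually, 1:1, stratified by medical school.
- Table 2, medical student outcome (ii): "Correlation between scores on the knowledge survey with patient quit rates".

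**The concern.** This is a partially nested design. Patients in the intervention arm are grouped under a counsellor; control patients are not. If students differ in how effective they are, outcomes of patients who share a student are positively correlated. The intervention arm's quit rate is then less precise than 415 independent patients would give. A sample size that ignores this overstates power on its own assumptions, by an amount that grows with the ICC, the number of patients per student and the unevenness of workloads.

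The article presents the programme as a potentially scalable model (Section 3), so the result is meant to carry over to other students. An interval for that purpose should include between-student variation.

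**Working it through.** **Inputs from the article.** Power 85%; alpha 0.05 (two-sided reproduces the figure); 20% versus 30%; attrition 20%; 415 per arm; at most 3 × 30 = 90 students. **Assumed, not in the article:** ICC 0.02 to 0.05; workload CV 0 (equal) or 0.7.

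**1. Reproduce 830.** With unpooled variance, n per arm = (1.960 + 1.036)² × (0.2×0.8 + 0.3×0.7) / 0.10² = 8.978 × 0.37 / 0.01 = 332.2. Taking 332, 332 / 0.8 = 415 per arm, or 830 in total. No design effect is included.

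**2. Patients per student.** 415 / 90 = 4.61 randomised; 332 / 90 = 3.69 evaluable. Both are minimum averages.

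**3. Design effect, intervention arm only.** DE = 1 + [m(1 + CV²) − 1] × ICC. For example, with m = 3.69, CV 0 and ICC 0.05, DE = 1 + 2.69 × 0.05 = 1.134.

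**4. Power.** SE = √{[p_C(1 − p_C) + DE × p_I(1 − p_I)] / n}; power = Φ(difference / SE − 1.96). Because Section 2.5 does not say whether 20% and 30% include losses, three bases are shown.

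| Basis | No clustering | CV 0, ICC 0.02 / 0.05 | CV 0.7, ICC 0.02 / 0.05 |
|---|---|---|---|
| 332 per arm, 20% v 30% (the plan's own calculation) | 85.0% | 83.9% / 82.3% (DE 1.054 / 1.134) | 83.2% / 80.5% (DE 1.090 / 1.225) |
| 415 per arm, 20% v 30% (rates already count losses as smokers) | 91.8% | 90.7% / 89.1% (DE 1.072 / 1.181) | 90.0% / 87.3% (DE 1.117 / 1.294) |
| 415 per arm, 16% v 24% (rates among those followed: 0.8 × 20%, 0.8 × 30%) | 82.5% | 81.0% / 78.7% | 80.0% / 76.4% |

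The pooled-variance formula agrees within about 0.3 percentage points. In the third row, the fall from 85% to 82.5% comes from counting losses as smokers and precedes any clustering.

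**5. Fewer counsellors.** If only 45 students counselled (an assumption), m = 332 / 45 = 7.38, and power on the first basis is about 82% (ICC 0.02) and 79% (ICC 0.05) with equal workloads.

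**6. If the primary analysis ignored counsellor.** The interval would need to be wider by the factor √[(0.16 + 0.21 × DE) / 0.37]: 1.5% wider at DE 1.054, up to 8.0% wider at DE 1.294. Two-sided type I error would be 2{1 − Φ[1.96 / √((1 + DE)/2)]}: 5.3% at DE 1.054, up to 6.7% at DE 1.294. The type I figures apply only under a null in which counsellors still differ and the average effect is zero.

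**The case against.** **The article does not commit to an unclustered analysis.** This stands. It names no primary model, and a condensed article may leave that to an analysis plan that is not shown. A reader might infer that the trial's interval will be too narrow and its type I error too high; the document supports only the conditional statement. The firm point is the sample size, which the article does state.

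**Type I error need not be inflated at all.** This also stands. Patients are randomised individually. If counselling affects no patient, students cannot create outcome differences and an unclustered test keeps its level. Inflation needs a null in which some students help, others harm, and the average is zero.

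**The attrition allowance may already absorb the design effect.** With losses counted as smokers, all 415 per arm are analysed. If 20% and 30% are rates on that definition, power is 91.8% unclustered and at least 87.3% across the scenarios in the table. This is a legitimate reading. The attrition inflation fits better with rates among those followed, but the article does not settle it. It is therefore not shown that the trial falls below 85%, only that its stated calculation leaves clustering out.

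**The lowest figures are not a clustering effect alone.** A reader might attribute the 76%-81% in the third row of the table to clustering. About 2.5 points of that fall come from the handling of losses, which is a separate issue.

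**The plan does not assume that students differ.** Listing a correlation between knowledge scores and quit rates asks a question; it does not presuppose the answer. Nor does Section 2.2.2 say outright that one student handles each patient throughout, although its wording suggests so. What remains is that the planned outcome makes between-student variation a live possibility in this trial.

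**Conclusion.** The point holds, at modest size. Nesting under at most 90 students in one arm is in the text, and 830 is the independent-patients figure. The direction of the effect follows for any ICC above zero; its size rests on an ICC and a workload spread that the article does not give. On the plan's own basis, clustering costs about 1 to 3 power points with equal workloads and about 2 to 4.5 with a workload CV of 0.7, over ICC 0.02 to 0.05. Whether power actually ends below 85% depends on what 20% and 30% mean. This should be corrected, but it does not threaten the trial's validity.

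**What to change.** 1. Record for each intervention patient which student counselled them. Student outcome (ii) in Table 2 needs this link as well, and it may be hard to reconstruct later.
2. Analyse the primary outcome at patient level with standard errors clustered on student in the intervention arm, each control being its own cluster, or with a partially nested mixed model. Include medical school, the randomisation stratum, as a fixed effect.
3. Report the counsellor ICC.
4. Restate power with the expected number of patients per student and a stated ICC range, applying the design effect to the intervention arm only, and say whether 20% and 30% count losses as smokers.

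The cost is a slightly wider confidence interval, a slightly lower stated power and one extra data field. No additional patients are needed.
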